### Recruitment and randomization

Part of the runners will be recruited from the PNMC program, which consists in 2–3 supervised running group-sessions of 10–20 runners per week, lasting 90 min each. Certified trainers lead these sessions, apply specific methodologies for running and for walking sessions. Prior to their enrollment, trainers must complete a training course. The other set of runners (which run freely, on their own) will be recruited from the community (recreational runners). To recruit this sample, we will use online advertisement and running events list servers, reach out for running clubs, and partnerships with both state and private organizations.

We will use a rolling recruitment strategy: participants will join the study as soon as they are considered eligible to facilitate management of available human resources. Each set of runners will be randomly assigned to the KoR intervention group or the control group general information group in a 1:1 ratio, stratified by group (PNMC and FRR). The method of randomized permuted blocks will be used, with random block lengths (4 or 6) (Broglio, 2018). Because participants will know which arm of the study they are in, blinding is not possible.

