**Figure 2. F0002:**
[figure not shown]
Organization of participant groups.

This approach was taken because (a) comparing runners belonging to PNMC with FRR (i.e. control group) allows examining the effect of the PNMC on behavior maintenance; (b) comparing FRR enrolled in the SRM intervention with FRR allows testing the effectiveness of a light-touch intervention on motivational and other psychological variables, and on behavior maintenance; and (c) comparing runners belonging to PNMC and receiving the SRM intervention with FRR receiving the SRM intervention will allows examining whether the SRM intervention has an additional effect on the study outcomes. Trial duration is one year with assessments at 6 weeks, and 6 and 12 months postbaseline (Figure 3).

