### Analytical strategy

Statistical analysis will be performed using SPSS Statistics version 25.0 (SPSS Inc., an IBM Company, Chicago IL, USA). Descriptive statistics will be calculated (mean, standard deviation and range). Repeated measures with Bonferroni corrections for adjusted comparisons will be used to examine differences between each intervention group(PNMC or SRM) and controls (i.e. free recreational runners), at all assessment points, in the primary and secondary outcomes measured. Statistical significance will be set at *p* < 0.05.

Mediation analysis, will test the psychological mechanisms underlying changes in running behavior from baseline to post program, 6 and 12 months. Multilevel modeling will be used to determine the SRM intervention effect on these motivational variables, with intervention group (SRM vs. Control group) as the between-subject factor and change in self-regulation and competence for running at baseline, 6–8 weeks, 6months and 12 months, serving as dependent variables. If necessary, multiple imputation methods will be implemented to provide robust results for primary and main secondary outcomes.

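### The stated PNMC-versus-free-runner analysis has no term for running group, so its standard errors are too small if outcomes correlate within PNMC groups

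*Protocol article*

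**What the plan says.** - **Grouping.** Recruitment and randomization describes PNMC as 2–3 "supervised running group-sessions of 10–20 runners per week", each lasting 90 minutes. On leadership it says: "Certified trainers lead these sessions, apply specific methodologies for running and for walking sessions". The comparison population is different: "The other set of runners (which run freely, on their own) will be recruited from the community (recreational runners").
- **Randomisation.** Within each population, individuals are allocated to SRM or no SRM "in a 1:1 ratio, stratified by group (PNMC and FRR"). Running group is not a stratum, and membership of PNMC is not randomised.
- **Comparisons.** Study design lists three. In (a), "comparing runners belonging to PNMC with FRR (i.e. control group) allows examining the effect of the PNMC on behavior maintenance". In (b), FRR with SRM is set against FRR without it. In (c), PNMC with SRM is set against FRR with SRM. Comparisons (a) and (c) put a PNMC arm against an FRR arm.
- **Model.** Analytical strategy states: "Repeated measures with Bonferroni corrections for adjusted comparisons will be used to examine differences between each intervention group(PNMC or SRM) and controls". No running-group or trainer effect is named. Multilevel modelling appears in the next paragraph, for the effect of SRM on motivational variables with SRM versus control as the factor. Running group is not named as a level there either.
- **Data and sample size.** The baseline data listed under Assessments and Data collection do not include running group. The sample size section gives no ICC and no design effect.

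**The concern.** Two of the four arms (110 of the planned 220 participants) train in groups and the other two do not, which makes the design partially nested. Shared sessions feed the primary outcome directly: 2–3 sessions of 90 minutes are 180–270 minutes a week on a common timetable. The article's own theory also treats relatedness as a driver of maintenance. Some positive correlation within PNMC groups is therefore plausible.

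If that correlation is ignored, the PNMC-versus-FRR comparisons get confidence intervals that are too narrow and p-values that are too small. Bonferroni correction does not help, because it adjusts for the number of tests and leaves the standard error of each test as it was. An effect of the PNMC programme could then be claimed on weaker evidence than the stated 5% level implies.

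**Working it through.** **Is any allowance already built in?** The article states 37 per group for d = 0.23 at p = 0.05, and 55 per group at baseline after 15% dropout. Dropout alone gives 37 / 0.85 = 43.5, so 44. The 37 is not the two-sample result either: 2 × (1.960 + 0.842)² / 0.23² ≈ 297 per group. That is a separate problem. What matters here is that the section states no clustering factor.

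**Inputs from the article:** session size 10–20; individual 1:1 randomisation within PNMC; 55 per arm; two-sided 5% level.

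**Inputs assumed:** ICC of the analysed outcome 0.01, 0.05 and 0.10; number m of analysed participants per running group in one arm. If every attendee of a 15-person group enrolled, 1:1 allocation would put m = 7.5 in each arm. Since 10–20 is session size and not enrolment, m = 3 is shown as a smaller case. Arms and groups are taken as equal in size, with equal total variance.

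**Formulas.** The design effect applies to the PNMC arm only:

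- DE = 1 + (m − 1) × ICC
- true variance / naive variance of the contrast, V = (DE + 1) / 2
- true type I error = 2 × [1 − Φ(1.96 / √V)]
- effective size of a PNMC arm = 55 / DE

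**Results**

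| m | ICC | DE | √V | Type I error | 55 worth |
|---|---|---|---|---|---|
| 3 | 0.01 | 1.02 | 1.005 | 5.1% | 53.9 |
| 3 | 0.05 | 1.10 | 1.025 | 5.6% | 50.0 |
| 3 | 0.10 | 1.20 | 1.049 | 6.2% | 45.8 |
| 7.5 | 0.01 | 1.065 | 1.016 | 5.4% | 51.6 |
| 7.5 | 0.05 | 1.325 | 1.078 | 6.9% | 41.5 |
| 7.5 | 0.10 | 1.65 | 1.151 | 8.9% | 33.3 |

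Worked line for m = 7.5 and ICC 0.05: DE = 1 + 6.5 × 0.05 = 1.325; V = 2.325 / 2 = 1.1625; √V = 1.078; 1.96 / 1.078 = 1.818; two-sided tail 6.9%. A simulation of the naive t test for this case (20,000 runs, 46 per arm) gave 7.1%.

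**Which ICC.** The Discussion makes change in running behaviour the dependent variable. Suppose a member of group g at time t has a shared component u_g + v_gt. The constant part u_g cancels from change since baseline; v_gt does not. The ICC in the table must therefore be read as that of the analysed quantity (change, or follow-up adjusted for baseline), which may differ from the ICC at a single visit.

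**SRM within PNMC.** Members of one running group are randomised to both arms, so the shared component enters both arm means and largely cancels from their difference. Ignoring the group does not shrink this standard error as it does for PNMC versus FRR.

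**The case against.** The strongest reply is that this is an omission in a condensed article: no sentence says that participants are treated as independent, and a fuller plan, not shown, could add a group term. It is true that independence is inferred from the named model. But the article does more than stay silent. It names the method for this comparison and assigns multilevel modelling to another question. A later analysis plan also cannot model running group unless it is recorded, and it is not in the listed baseline data.

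Several stronger readings are tempting and are not supported:

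- *Whole groups of 15 as clusters within an arm.* A reader might take m = 15 and infer error rates of 5.8 / 9.2 / 13.3%, with 55 runners worth about 32. Those figures ignore that 1:1 allocation splits each group between two arms, and they need nearly every attendee to enrol. The eligibility limits (at most 3 months of running, at least 60 minutes of vigorous activity a week) and rolling recruitment make full enrolment unlikely.
- *A fixed trainer and fixed companions.* The article says that sessions are trainer-led. It does not say that membership or trainer is constant.
- *Harm to the SRM result generally.* The trial's main hypothesis concerns SRM, which is randomised within PNMC and within FRR. That contrast is not undermined by this point.

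It is also fair to say that self-selection is the larger threat to PNMC versus FRR. A correct standard error does not remove that bias, but the bias does not excuse an interval that is too narrow.

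**Conclusion.** The concern holds for contrasts that set a PNMC arm against an FRR arm, including PNMC with SRM against FRR with SRM. The direction is certain for any positive within-group correlation in the analysed outcome. The size is not known from the article. Over the assumed ICC of 0.01–0.10, the true type I error of a nominal 5% test runs from 5.1% to 6.2% with 3 analysed per group per arm and from 5.4% to 8.9% with 7.5. At ICC 0.05 with 7.5 per group, 55 PNMC runners are worth about 42 independent ones. The effect is thus negligible to moderate, and largest if whole PNMC groups enrol. Under the planned Bonferroni adjustment the nominal level is lower, but inflation remains.

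**What to change.** Record each PNMC participant's running group, and trainer, at baseline.

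For every PNMC-versus-FRR contrast, specify a partially nested mixed model: a running-group random effect in the PNMC arms only, with free runners as individuals, and small-sample degrees of freedom. With 55 in an arm there would be only about 7 groups at 7.5 each (55 / 7.5) or 18 at 3 each (55 / 3), so large-sample tests are not safe.

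The random effect must act on the analysed contrast. Use either a group-by-time random effect in the repeated-measures model, or a group random intercept in a model of follow-up adjusted for baseline. A plain group intercept on the repeated outcomes is not enough, because it cancels from change.

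The cost is one or two recorded variables and a few lines of analysis text, a wider but correct interval, and some lost degrees of freedom, which can reduce precision if the ICC is near zero. The change leaves the non-randomised nature of PNMC versus FRR untouched.

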### Assessments

Data on demographics (age, gender, date of birth, education, income, employment, marital status, weight, height, physical activity history, and personal characteristics) and potential psychological moderators (i.e. index of autonomous functioning) will be collected only at baseline.

The primary outcome of this study is running behavior, which will be measured at baseline, intervention's end and 6-month follow-up by self-report (frequency and minutes of running per week). At 12 months, participants will be asked by telephone whether they keep running (at least) at their initial level, or not.

Secondary outcomes will include putative mediators and outcomes. Basic psychologic need satisfaction will be assessed via the Psychological Need Satisfaction in Exercise Scale (Wilson, Rogers, Rodgers, & Wild, 2006); Basic psychological need frustration will be assessed trough the Basic Psychological Need Frustration in Exercise Scale (Chen et al., 2015); Motives and gains via Exercise Motives and Gains Inventory (Ingledew, Markland, & Strömmer, 2014); Behavioral regulations will be assessed via the Behavioral Regulation in Exercise Questionnaire – 3 (Cid et al., 2018); Self-determination trait will be assessed via the Index of Autonomy Functioning (Weinstein, Przybylski, & Ryan, 2012); Self-regulation skills will be measured trough the Action planning, Coping planning, and Action control scales (Sniehotta, Scholz, & Schwarzer, 2005a; Sniehotta, Schwarzer, Scholz, & Schuz, 2005b); Self-efficacy will be assessed via the Modified Bandura's Exercise Self-Efficacy Scale (Bandura, 1997); Automaticity will be measured trough the Self-Report Behavioural Automaticity Index (Gardner & Tang, 2014; Gardner, Abraham, Lally, & de Bruijn, 2012); and exercise identity via the Exercise Identity Scale (Anderson & Cychosz, 1994). Regarding psychological outcomes, flow will be measured through the Dispositional Flow Scale – 2 in Exercise (Jackson & Eklund, 2002); Vitality will be assessed through the Subjective Vitality Scale (Ryan & Frederick, 1997); and passion through the Passion Scale (Cid et al., 2019).

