### Data collection

Participants will go through four assessment periods at baseline, 6 weeks (post-program), 6 months, and 12 months follow-up. The training and clarification session will be completed by telephone to ensure participants are equipped with the skills to access the intervention contents. Before the first, third and fourth assessment periods, eligibility will be checked against inclusion and exclusion criteria through a telephone screening/re-screening call, 1 week prior to each visit. Participant's timeline is shown in Figure 3.

*Assessment* 1 (baseline): Clarification session about the study. If participants are still interested in enrolling in the study, eligibility will be checked, and they will be asked to fill out an informed consent form. Randomization and allocation to one of the four arms of the trial will be performed. Data on demographics and potential psychological moderators will be collected. A battery of psychological and behavioral questionnaires will be completed online using google forms (in one-week time) – running behavior (i.e. frequency and minutes per week), motivations, basic psychological needs, motives and gains, self-regulation skills, passion, flow, and vitality. This task is estimated to take approximately 1 h, but participants will be able to do breaks and return later to complete the psychometric evaluation during that week. Debrief on how to use the KOR web-based intervention content – the toolkit (approximately 1 h).

*Assessment*s 2 and 3 (intervention's end and 6-month follow-up). Email reminder prior to this evaluation period will be sent. The same battery of psychological and behavioral questionnaires will be completed online using google forms (in one-week time) – running behavior (i.e. frequency and minutes per week), motivations, basic psychological needs, motives and gains, self-regulation skills, passion, flow, and vitality –, and will take approximately 1 h.

*Assessment* 4 (12-month follow-up). Running behavior maintenance will be assessed through a telephone call, asking participants whether they keep running at their initial level or higher, or not.

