### Power calculations and sample size estimation

Two types of sample size calculations were made: (a) using the primary outcome – running minutes and (b) using secondary outcomes, in particular, changes on key psychosocial variables. Regarding our primary outcome, we have used vigorous physical activity for our calculations. A small effect size (Cohen's *d *= 0.23) is expected, a value previously registered in studies with intrinsic motivation interventions (Ntoumanis et al., 2020; Sheeran et al., 2020). Considering a power of 0.8 with two-tailed analysis, we estimated that each intervention group should have 37 (*p *= 0.05) or 55 participants (*p *= 0.01). Concerning our secondary outcomes, we are expecting effects sizes ranging from 0.23 to 0.73, based on previous reports (Ntoumanis et al., 2020; Sheeran et al., 2020). Thus, assuming an effect size of 0.50, 18 subjects/group will be required to detect significant differences at *p *= 0.05 and 28 for *p *= 0.01. Given that the primary outcome is expected to have a smaller effect size, and expecting a dropout rate of 15% at follow-up, we estimate that approximately 55 subjects/group are needed at baseline (for *p *= 0.05). Thus, recruiting 220 participants will ensure high statistical power for our primary analyses, extending its power to the secondary analyses.

Trial results will be published in peer-reviewed scientific journals and in several international and national scientific conferences. The website will be our central media to promote the dissemination of the results to the general public. Other media will be reached through university partners and website.

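### The primary outcome is two unranked measures in one section and running minutes alone in another, and the stated Bonferroni correction is not tied to either version

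*Protocol article*

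**What the plan says.** Four sections of the protocol article bear on this.

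- **Assessments.** The primary outcome is running behavior, measured at baseline, intervention's end and 6 months "by self-report (frequency and minutes of running per week". The two measures are not ranked. The next sentence, still ahead of the secondary outcomes, changes the variable: "At 12 months, participants will be asked by telephone whether they keep running (at least) at their initial level, or not".
- **Data collection.** The last assessment collects only that answer: "Running behavior maintenance will be assessed through a telephone call". Minutes and frequency are not collected at 12 months.
- **Analytical strategy.** "Repeated measures with Bonferroni corrections for adjusted comparisons will be used" to examine "differences between each intervention group(PNMC or SRM) and controls", "at all assessment points, in the primary and secondary outcomes measured". Significance is set at p < 0.05. The set of tests that the correction covers is not given.
- **Power calculations and sample size estimation.** One calculation is made "using the primary outcome – running minutes", although "we have used vigorous physical activity for our calculations". It gives 37 per group at p = 0.05 and 55 at p = 0.01. After a 15% dropout allowance the plan is 55 per group, labelled as for p = 0.05, and 220 in total.

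**The concern.** Assessments and the power section disagree on whether the primary outcome is one measure or two, and no section says which visit decides the trial. If minutes and frequency are each analysed in their own model at 5%, the trial has two routes to a positive primary result, and a third if the 12-month answer is treated as primary. The 5% level then applies to each model and not to the primary claim. The choice of headline measure could also be made after the data are seen. That matters more than usual here because participants know their arm and running is self-reported.

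**Working it through.** **1. The plan's own figure.** The inputs from the power section are d = 0.23, two-sided 0.05 and power 0.80. For two independent groups, n = 2(z₁₋α/₂ + z₀.₈)²/d² = 2 × 7.849/0.0529 = 296.7, so 297 per group. The stated 37 is not reproduced by this formula. That is a separate and larger problem. Here only the relative cost of extra primary tests is used (step 5).

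**2. How many primary tests remain.** On the natural reading, Bonferroni handles group and visit comparisons inside one repeated-measures model.

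- Minutes and frequency are different variables, so they need two models.
- The 12-month yes/no answer cannot enter either model, because neither variable is collected then. It needs its own test.
- So k = 2 if the 12-month answer is not primary, and k = 3 if it is.

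**3. Chance of at least one false positive, each model held at 5%.** For independent tests it is 1 − 0.95ᵏ:

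- k = 2: 1 − 0.9025 = 9.8%
- k = 3: 1 − 0.8574 = 14.3%

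For tests with common correlation ρ it is 1 − ∫φ(u)[Φ((1.96 − √ρ·u)/√(1−ρ)) − Φ((−1.96 − √ρ·u)/√(1−ρ))]ᵏ du. The documents give no correlation, so ρ is an assumption.

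| ρ | k = 2 | k = 3 |
|---|---|---|
| 0 | 9.8% | 14.3% |
| 0.5 | 9.1% | 12.5% |
| 0.7 | 8.3% | 10.9% |
| 0.9 | 7.0% | 8.4% |

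This treats each model as using its full 5% and the 12-month answer as approximately normal. Whatever the correlation, the rate cannot exceed 2 × 5% = 10% or 3 × 5% = 15%.

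**4. The other reading.** If the correction spans every primary test, the rate is at most 5%. The wording does not exclude this.

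**5. Cost of splitting alpha.** The required n scales with (z₁₋α/₂ + z₀.₈)²:

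- one test, α = 0.05: 7.849
- two tests, α = 0.025: 9.505, a ratio of 1.21
- three tests, α = 0.0167: 10.469, a ratio of 1.33

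At d = 0.23 this gives 297, 360 and 396 per group before dropout. On the plan's own base it gives 37, then 37 × 1.21 = 45, then 37 × 1.33 = 50 (rounded up). The power section mentions no such allowance.

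**The case against.** Several points on the other side are fair.

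- **A correction is stated.** A reader might infer that each measure is tested at 5% at every visit without adjustment: two measures at two visits plus the 12-month answer, five tests per contrast. That would give about 15–23% (correlations 0.7 to 0). The document does not support this, because it prescribes Bonferroni for comparisons across assessment points. Nor does it establish an error rate well above 5%, since the family is undefined. This stands.
- **A primary measure is named.** The power section says minutes, so it would be wrong to say that none is named. What stands is that Assessments says otherwise, and the Discussion again lists both as dependent variables.
- **The 12-month answer may not be primary.** It has its own sentence without that label. But it sits in the primary-outcome paragraph, and maintenance is the trial's stated target. Its status is unclear, so both k = 2 and k = 3 are shown.
- **An article may leave the deciding visit and the correction family to the full protocol or analysis plan.** This is accepted; their absence alone would be no finding. The conflict between two stated definitions of the primary outcome is not an omission.
- **55 per group might already cover multiplicity,** since it equals the p = 0.01 figure. The section labels it p = 0.05 and ties it to dropout and the smaller primary effect. On the plan's own base, 55 × 0.85 = 46.75 completers would exceed 45 but not 50. That is incidental, and the base of 37 does not follow from d = 0.23.

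**Conclusion.** The point holds as an inconsistency in stated text. The primary outcome is two unranked measures in Assessments and one measure in the power section. The comparisons cover all assessments without a deciding visit, and the correction is not tied to a defined set of primary tests. On the natural within-model reading, the false-positive rate for the primary outcome is about 8–10% with two measures and 11–14% with three, for assumed correlations of 0 to 0.7. Weekly minutes and weekly frequency of the same activity may correlate more strongly; at 0.9 the figures fall to about 7% and 8%. If Bonferroni spans all primary tests the rate is at most 5%, but the sample size then has to be restated at the smaller alpha. The plan should be changed. The defect is moderate, and it is smaller than the sample-size arithmetic problem noted in the first step of the check.

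**What to change.** Make Assessments agree with the power section:

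- Name running minutes per week as the only primary measure.
- Prespecify one deciding visit. Six months is an example, being the last visit at which minutes are collected.
- Prespecify one deciding contrast. SRM versus no SRM is an example, because that is what is randomised, within PNMC and within free runners.
- Label frequency, the other visits and the 12-month answer as secondary.

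The visit and contrast are proposals. The power section names neither, and any single choice made before the data are seen would cure the defect. Choosing 6 months in a one-year maintenance trial needs a sentence of justification.

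If more than one primary test is kept, state that Bonferroni spans all of them and restate the sample size at the reduced alpha (about 21% more participants for two tests, 33% for three).

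The cost is a sentence in Assessments and one in Analytical strategy, with no new data. The downside is that frequency, the other visits and the PNMC comparison lose primary status.

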### Eligibility criteria

*Inclusion criteria*: age between 18 and 65 years; running for no longer than 3 months; performing a minimum of 60 min of vigorous physical activity per week; being free from major orthopedic limitations (defined as those which would limit moderate to vigorous physical activity (MVPA)); and from clinical diagnosis with any condition that may interfere with performing MVPA; being free from untreated or major psychological disorders (e.g. psychosis, clinical depression); and possessing or willing to acquire a smartphone or computer with internet access.

*Exclusion criteria*: inability to provide written informed consent; inability to follow written material or telephone conversations in Portuguese that would preclude completion of study questionnaires and use of the digital intervention (i.e. KOR toolkit, see below); intention of pregnancy in the next 12 months; planning to travel for more than 2 weeks in the next 12 months or to emigrate; suffering any injury in the course of the study.

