## Discussion

This paper presents the rationale, development, study design, methods and pilot application of the KOR trial, aimed at testing the effect of the intervention on the maintenance of recreational running behavior over time, after being voluntarily initiated by community-dwelling adults in the previous 3 months. This ‘light-touch’ intervention is unique in that it approaches running behavior and its sustainability, delivered in a digital format, and based on strong theoretical foundations.

We hypothesize that the sustainability of running behaviors will be higher in the SRM groups compared to the control group. Change in running behavior (e.g. frequency and minutes of running per week) and secondary outcomes related to the quality of the running experience (e.g. passion, flow, vitality) will be used as the dependent variables.

Additionally, the results of the pilot feasibility study, intended at testing intervention adherence, participant satisfaction, and questionnaire acceptance, were also presented. Overall, the pilot study indicated that the intervention has good acceptability, feedback was very positive, but toolkit interaction decreased after the first weeks, which is common in web-based interventions (Baumel & Yom-Tov, 2018). Moreover, the generalized use of other running-related devices, applications and communities may have overlapped with the anticipated content of the toolkit, challenging participants’ interaction. The completion ratio of the post-program questionnaire was low, maybe due to its extension and burden, but also because its timeline ended near the summer break.

The main trial should reduce questionnaire length and burden, and include interface with usual monitoring gadgets and apps (APIs), to increase data detail and prevent ‘unnecessary’ data insertion by the participants. Features such as feedback and social sharing, added to the goal setting features already integrated in the toolkit, may also increase attractiveness (Hosseinpour & Terlutter, 2019).

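### At 12 months the primary outcome becomes one self-judged yes/no answer, although the two running items used at the other assessments could be asked in the same call (cheap improvement)

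*Protocol article*

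**What the plan says.** Protocol article, Assessments: running behavior is the primary outcome, measured "by self-report (frequency and minutes of running per week") at baseline, at the end of the intervention and at 6 months. For the last assessment the same paragraph changes the measure: "At 12 months, participants will be asked by telephone whether they keep running (at least) at their initial level, or not". Data collection (Assessment 4) repeats this as a telephone question on "whether they keep running at their initial level or higher, or not". Neither section says whether the initial level means frequency or minutes, what period the answer covers, whether the recorded baseline value is read back, or whether any shortfall is tolerated.

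Analytical strategy plans repeated-measures comparisons with controls at every assessment point for primary and secondary outcomes. It also plans a mediation analysis of change in running behavior from baseline to post-program, 6 and 12 months. Recruitment and randomization states that blinding is not possible. The Discussion gives the hypothesis: "We hypothesize that the sustainability of running behaviors will be higher in the SRM groups compared to the control group".

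**The concern.** The 12-month assessment is the longest view of maintenance that the trial offers, and it is where the outcome carries least information. Three things follow.

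- **Coarseness.** A runner a little below the starting level and a runner who has stopped get the same code.
- **Possible misclassification.** The cut-off sits exactly at each person's own starting level. A runner whose usual level has not changed may answer no after an ordinary light spell.
- **Break in scale.** A binary answer cannot be the fourth value in a series of minutes or sessions per week. As written, the planned comparison at every assessment and the mediation of change to 12 months have no 12-month value on the scale of the other three.

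At stake is whether the trial can say how much running was retained at one year in each arm, rather than only how many participants said yes.

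**Working it through.** **1. The plan's own figures.** There is none to reproduce on this point. The documents give no 12-month maintenance rate, week-to-week variability or misclassification rate, and the sample size was set on running minutes. Every variability figure below is an assumption.

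**2. Measure against analysis.**

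| Assessment | Running measure | In the repeated-measures plan | Endpoint of change in mediation |
|---|---|---|---|
| Baseline | frequency, minutes/week | yes | reference |
| 6 weeks | frequency, minutes/week | yes | yes |
| 6 months | frequency, minutes/week | yes | yes |
| 12 months | yes/no against initial level | yes | yes |

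The last row does not fit the other three. This part needs no assumption.

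**3. Share of unchanged runners coded as not maintaining.** Suppose the answer behaved like a comparison of two independent reports. Assume a constant true level of 120 min/week and lognormal within-person variation with a coefficient of variation (CV) of 10% to 50%. The quantity is P(12-month report < baseline report), by simulation with 1,000,000 draws.

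| How the reports behave | Share coded as not maintaining |
|---|---|
| Continuous, strict comparison | 0.50 at every CV |
| Rounded to 15 min | 0.33 (CV 10%) to 0.46 (CV 50%) |
| Rounded to 30 min | 0.18 (CV 10%) to about 0.41 (CV 50%) |
| Whole sessions per week | 0.33 to 0.34 |
| Continuous, entry only if baseline is at least 60 min, usual level varying between people | 0.54 (CV 20%) to 0.62 (CV 50%) |

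The span is about 18% to 62%. The last row depends on how close usual levels lie to the floor. With median 120 min and between-person log-SD 0.5, the shares are 0.515, 0.527 and 0.544 at CV 15%, 25% and 40%. That row also applies the floor to running minutes, whereas Eligibility criteria sets it on vigorous activity: "performing a minimum of 60 min of vigorous physical activity per week".

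**4. Effect on a difference between arms.** Let Se be the chance that a true maintainer is coded as maintaining, and Sp the chance that a true relapser is coded as not maintaining. If both are equal in the two arms:

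observed difference = (Se + Sp − 1) × true difference.

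- All maintainers exactly unchanged, Se = 0.50, Sp = 1: factor 0.50.
- Half of maintainers unchanged and half increased, with the latter coded correctly 90% of the time: Se = 0.5 × 0.5 + 0.5 × 0.9 = 0.70, so the factor with Sp = 1 is 0.70.
- All maintainers increased: Se = 0.90, factor 0.90.
- Relapsers down by only 25% at CV 30%: they pass 24.4% of the time, so Sp = 0.756. With Se = 0.50 the factor is 0.50 + 0.756 − 1 = 0.256.

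The span is about 0.26 to 0.90.

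**5. Illustration of cost.** With 55 per group and 15% dropout, 55 × 0.85 = 46.75, about 47 per arm. Assume true maintenance of 70% against 50%, a two-sided 0.05 level and the normal approximation for two proportions.

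| Se (Sp = 1) | Observed rates | Power, 47 per arm | n per arm for 80% power |
|---|---|---|---|
| 1.00 | 70% v 50% | 0.51 | 93 |
| 0.75 | 52.5% v 37.5% | 0.31 | 172 |
| 0.50 | 35% v 25% | 0.18 | 329 |

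Even without misclassification this binary comparison has power of only 0.51 in the example.

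**6. Direction.** The identity in step 4 fails if answering differs by arm, which is possible without blinding. With equal true maintenance of 60%, Sp = 1, and Se of 0.80 in one arm and 0.70 in the other, the observed rates are 0.60 × 0.80 = 48% and 0.60 × 0.70 = 42%. That is a spurious 6-point difference.

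**The case against.** The strongest reply is that steps 3 and 4 model a measurement the protocol does not make. Nobody compares two noisy weekly reports. The participant judges a level, and equality counts as maintained, so someone who knows their routine is unchanged would naturally say yes. Ties are likely, because frequency is one of the two items and the organized program runs fixed sessions two or three times a week. Entrants have been "running for no longer than 3 months", so many who continue may have increased, and they count as maintaining too. All of this stands.

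A reader might therefore infer from the zero-margin cut-off that about half of stable runners would fail and that a true difference would be roughly halved. The documents do not support that. It needs strict comparison of continuous reports with equal error, every maintainer exactly unchanged, every relapser answering no, and no difference in answering between arms. Even the 18% to 62% range is conditional on the two-report model and is not a bound.

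It can also be said that running at or above the starting level is a coherent definition of maintenance, that call scripts usually belong in the full protocol, and that the sample size does not rest on this item. These are fair and keep the point modest. A short call also has merit: in the pilot 83.3% found the questionnaire too long, and 7 of 18 completed the post-program questionnaire. But the article states the binary question twice, states the analyses it is meant to serve, and the two do not match. Self-judgement does not remove the tolerance question; it leaves each participant to set a tolerance privately.

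**Conclusion.** The point holds as a cheap improvement. Two parts rest on the text alone: the 12-month running outcome is a single self-judged, unblinded yes/no answer, and it cannot enter on the same scale the analyses that Analytical strategy extends to 12 months. That the answer merges small declines with stopping follows from the wording. That it misclassifies some stable runners is plausible but not measurable from the documents.

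Under the assumed variability, 18% to 62% of unchanged runners could be coded as not maintaining, and the multiplier on a true difference runs from 0.26 to 0.90 when errors are equal in the arms. With unequal errors, dilution is not assured and the bias can go either way. The case for changing the question does not depend on where in those ranges the truth lies.

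**What to change.** In the 12-month call already planned, ask the same frequency and minutes-per-week items as at the other assessments, over the same reference period, and state that period. Compare arms on the 12-month value adjusted for baseline. That value can then also serve the repeated-measures and mediation analyses.

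Keep the yes/no maintenance answer as supportive, and say whether the initial level means frequency or minutes and whether the recorded baseline is read to the participant. If a tolerance is wanted, define it as a fraction of recorded baseline minutes, fix it before the data are seen and report it as an optional sensitivity analysis. Any particular fraction is a convention and would count some real declines as maintained, so none is required here.

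The cost is two extra questions in the call and a slightly longer analysis section. The change does not cure everything: the data remain unblinded self-report, and the 12-month items would be answered by telephone rather than online, although in the same way in all arms.
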